### 11.3 Participant completed Questionnaires

A list of participant-completed forms can be found in Table 10.

**Table 10:** A list of participant completed questionnaires

| Name of questionnaires                                 |
|--------------------------------------------------------|
| Speech, Spatial and Qualities of hear scale (SSQ)      |
| Vestibular Rehabilitation Benefit Questionnaire (VRBQ) |
| Tinnitus Functional Index (TFI)                        |
| Health Utilities Index 3 (HUI3)                        |
| ICECAP-A                                               |

All participant questionnaires will be completed by participants in the clinic, overseen by site staff. Questionnaires should generally be completed by the participant alone, however physical assistance in completing the form can be given by the research staff or the participant's friends and relatives where appropriate. In such circumstances, questions are to be read to the participant verbatim and responses must not be led by the person assisting with the form completion. This requirement must be made clear when the participant's friends and relatives are providing the assistance. Participants should be encouraged to respond to all questions but can refuse to answer any, or all, of the questions should they wish. Where any questions are unanswered, research site staff should clarify with the participant that they have chosen not to respond specifically to the unanswered questions and that they have not simply missed them in error.

#### **11.4 Home hearing test submission**

Participants that consent to perform weekly hearing tests at home will access an online platform (HearX software) via the trial website in order to perform the hearing tests and submit their results. Participants will use their unique identification number to identify themselves. Data from the digits in noise test, pure tone thresholds and dizziness and tinnitus visual analogue scores will be collected, stored in the hearX server and transferred to BCTU by API or csv file.

#### **11.5 Data Management**

Processes will be employed to facilitate the accuracy and completeness of the data included in the final report. These processes will be detailed in the trial specific Data Management Plan (DMP) and include the processes of data entry and data queries.

Data entry will be completed by the site staff via a bespoke BCTU trial system with the exception of participant completed booklets which will be entered by BCTU staff. The data capture system will conduct automatic range checks for specific data values to ensure high levels of data quality. Queries will be raised using DCFs via the trial system, with the expectation that these queries will be completed by the site within 30 days of receipt. Overdue data entry and data queries will be requested on a monthly basis.

---

## 11.6 Data Security

The University of Birmingham has policies in place, which are designed to protect the security, accuracy, integrity and confidentiality of Personal Data.

The trial will be registered with the Data Protection Officer at UoB and will hold data in accordance with the Data Protection Act (2018 and subsequent amendments). BCTU has arrangements in place for the secure storage and processing of the trial data, which comply with UoB policies.

The Trial Database System incorporates the following security countermeasures:

- Physical security measures: restricted access to the building, supervised onsite repairs and storages of back-up tapes/disks are stored in a fireproof safe.
- Logical measures for access control and privilege management: including restricted accessibility, access controlled servers, separate controls of non-identifiable data.
- Network security measures: including site firewalls, antivirus software and separate secure network protected hosting.
- System Management: the System will be developed by the Programming Team at BCTU, and will be implemented and maintained by the Programming Team.
- System Design: the system will consist of a database and a data entry application with firewalls, restricted access, encryption and role based security controls.
- Operational Processes: the data will be processed and stored within BCTU. Anonymised data entered by the participant is submitted from the client-side browser to HearX servers to store the tests. No data leaves the HearX servers except for API/csv download directly to BCTU.
- System Audit: The System will benefit from the following internal/external audit arrangements:
  - Internal audit of the system
  - Periodic IT risk assessment
- Data Protection Registration: The UoB's Data Protection Registration number is Z6195856.

## 11.7 Archiving

All records created by following trial procedures and all documents listed in guidance relating to the conduct of the trial must be retained and archived for the specified period.

The TMF is normally composed of a sponsor file, held by the sponsor organisation, and an investigator site file, held by the site investigator. Documents are archived following regulatory requirements and local procedures.

Retained data should still be accurate, accessible and stored securely and confidentially.

It is the responsibility of the PI to ensure all essential trial documentation and source documents (e.g. signed ICFs, ISFs, participants' hospital notes, CRFs etc.) at their site are securely retained for the contractual period. Archiving will be authorised by BCTU on behalf of UoB following submission of the end of trial report. No documents should be destroyed without prior approval from the BCTU Director or their delegate.

---

The TMF will be stored at BCTU for at least 3 years after the end of the study. Long-term offsite data archiving facilities will be considered for storage after this time; data will be stored securely and confidentially for at least 25 years. BCTU has standard processes for both hard copy and computer database legacy archiving.

## 12 QUALITY CONTROL AND QUALITY ASSURANCE

### 12.1 Site Set-up and Initiation

All local PIs will be asked to sign the necessary agreements, including a **STARFISH Site Signature and Delegation log**, between the PI and BCTU and supply a current CV and GCP certificate. All members of the site research team are required to sign the Site Signature and Delegation Log, which details which tasks have been delegated to them by the PI. The Site Signature and Delegation Log should be kept up to date by the PI. It is the PI's responsibility to inform BCTU of any changes in the site research team.

Prior to commencing recruitment, each site will undergo a process of initiation, either a meeting or a tele/video conference, at which key members of the site research team are required to attend, covering aspects of the trial design, protocol procedures, adverse event reporting, collection and reporting of data and record keeping.

BCTU will provide each site with an ISF containing essential documentation, instructions, and other documentation required for the conduct of the trial. The PI or delegate is required to keep the ISF up to date throughout the trial.

### 12.2 Monitoring

The central and on-site monitoring requirements for this trial have been developed in conjunction with the trial specific risk assessment and are documented in the trial specific monitoring plan.

#### 12.2.1 Onsite Monitoring

All sites will be monitored in accordance with the trial specific risk assessment and monitoring plan. Any monitoring activities will be reported to BCTU and any issues noted will be followed up to resolution. Additional on-site monitoring visits may be triggered. PIs and site research team will allow the BCTU staff access to source documents as requested. The monitoring will be conducted by BCTU/UoB staff.

#### 12.2.2 Central Monitoring

BCTU will check received ICFs and CRFs for compliance with the protocol, data consistency, missing data and timing at a frequency and intensity as determined by the DMP. Sites will be sent DCFs requesting missing data or clarification of inconsistencies or discrepancies.

### 12.3 Audit and Inspection

The Investigator will permit trial-related monitoring, audits, ethical review, and regulatory inspection(s) at their site, providing direct access to source data/documents. The investigator will comply with these visits and any required follow up. Sites are also requested to notify BCTU of any relevant inspections or local audits.

---

## 12.4 Notification of Serious Breaches

In accordance with the Medicines for Human Use (Clinical Trials) Regulations 2004 and its amendments, the Sponsor of the trial is responsible for notifying the licensing authority in writing of any serious breach of the conditions and principles of GCP in connection with that trial or the protocol relating to that trial, within 7 days of becoming aware of that breach.

For the purposes of this regulation, a “serious breach” is a breach which is likely to affect;

- the safety or physical or mental integrity of the participants of the trial;
- the scientific value of the trial

Sites are therefore requested to notify BCTU of any suspected trial-related serious breach of GCP and/or the trial protocol as soon as they become aware of them. Where BCTU is investigating whether or not a serious breach has occurred, sites are also requested to cooperate with BCTU in providing sufficient information to report the breach to the MHRA where required and in undertaking any corrective and/or preventive action.

Sites may be suspended from further recruitment in the event of serious and persistent non-compliance with the protocol and/or GCP, and/or poor recruitment.

## 13 END OF TRIAL DEFINITION

The end of trial will be the date of the last data capture including resolution of DCFs. This will allow sufficient time for the completion of protocol procedures, data collection and data cleaning. BCTU will notify the Sponsor, MHRA and REC within 90 days of the end of the trial. Where the trial has terminated early, BCTU will inform the MHRA and REC within 15 days of the end of trial. BCTU will provide Sponsor, MHRA and REC with a summary of the clinical trial report within 12 months of the end of trial.

## 14 STATISTICAL CONSIDERATIONS

### 14.1 Sample size

Sample size has been calculated based on the primary outcome measure of absolute improvement in pure-tone audiogram. A typical gain in hearing threshold in the control group (oral steroid only) would be 25 dBHL, with standard deviation (SD) of 25 dBHL (2). As specified in published international criteria for ISSNHL (2), we have defined 10 dBHL as a minimum clinically important difference (MCID) for the sample size.

With 90% power and alpha of 0.025 (for the 3-arm trial design with two key group comparisons; see below), to observe a MCID of 10 dBHL with SD of 25 dBHL, the trial will require 157 participants per arm, or 471 participants in total. After allowing for a 10% attrition rate this gives a sample size of 175 per arm, or 525 in total for a 3-arm study.

#### Key secondary outcome on spatial hearing:

The secondary outcome of SSQ is validated to assess the disability associated with unilateral hearing loss seen in ISSNHL, and provides an additional measure of functional hearing for which the study is adequately powered. The mean SSQ total score for the control group (oral steroid only) is expected to approximate 4 points based on the average scores for an equivalent group in our own clinical sample (n=145 adults), with SD of 1.9 (19,27). A difference of 0.65 points for the SSQ total score has been defined as the MCID (19,27).

---

For the SSQ secondary outcome measure, 471 participants (525 recruitment target allowing for 10% attrition rate) will provide just under 80% power (alpha of 0.025, for the 3-arm trial design with two key group comparisons) to observe a MCID of 0.65 points with SD of 1.9 (effect size approximately 1/3 SD). The trial is therefore also adequately powered to demonstrate a difference in SSQ scores between intervention arms, complementing the primary outcome by indicating the difference in disability and functional impact of hearing recovery between interventions.

## 14.2 Analysis of outcomes

A separate Statistical Analysis Plan (SAP) will be produced and will provide a more comprehensive description of the planned statistical analyses. The reporting of the outcomes will be based on the guidelines as published in the Reporting of multi-arm parallel-group randomised trials (22). A brief outline of these analyses is given below.

The objective of the trial is to test the superiority of three interventions:

- Oral steroid
- Intratympanic steroid
- Combination oral and intratympanic steroid

All analysis will have the following two key group comparisons:

- Intratympanic steroid versus oral steroid
- Combination oral and intratympanic steroid versus oral steroid

Oral steroid group will be considered as the control group, i.e. reference category for all analyses. A comparison of intratympanic steroid versus combination oral and intratympanic steroid will also be performed as part of an exploratory analysis for all outcomes.

All primary analyses (primary and secondary outcomes including safety outcomes) will be by intention-to-treat (ITT), i.e. all participants will be analysed in the intervention group to which they were randomised irrespective of adherence to randomised intervention or other protocol deviation. As a secondary (or sensitivity) analysis, a per-protocol analysis will also be carried out for the primary outcome.

To maintain an overall 5% type I error rate, each comparison will be tested at a significance level of 2.5% to account for the increase in the risk of type I error associated with making two key comparisons. Therefore, for the primary outcome and all other secondary outcomes measures, a Bonferroni correction (23) will be applied to account for the increase in the risk of type I error associated with making two key comparisons (i.e. “intratympanic steroid versus oral steroid” and “combination oral and intratympanic steroid versus oral steroid”).

For all outcome measures, appropriate summary statistics and differences between groups, e.g. mean differences, relative risks, absolute differences will be presented, with two-sided 97.5% confidence intervals. Outcomes will be adjusted for the minimisation variables listed in section 6.4.3 and any baseline values (where applicable).

### 14.2.1 Primary outcome

The primary outcome is the absolute improvement in pure tone audiogram average at 12-week following randomisation (calculated at 0.5, 1.0, 2.0, 4.0 kHz). This data is collected at

---

baseline and at each follow-up visit. The data for this outcome is continuous and therefore will be summarised using the mean and standard deviation along with minimum and maximum values with respect to the intervention arms and overall at each time-point.

Difference between group means and associated 97.5% confidence intervals at each time-point will be estimated through the use of a repeated measures mixed-effects linear regression model. All assessment times (baseline and the post-treatment time points) will be included. Parameters allowing for participant, treatment group, time variable, the randomisation minimisation variables and the baseline score will be included (all as fixed effects). Time will be assumed to be a categorical (fixed) variable. To allow for a varying treatment effect over time, a time by treatment interaction parameter will be included in the model. Estimates of differences between groups at the 6 week and 12 week time-point will be taken from the model including this interaction parameter. Results will be presented as adjusted mean difference and 97.5% confidence interval. Longitudinal plots of the data over time will be constructed for visual presentation of the data.

#### 14.2.2 Secondary outcomes

The secondary outcomes consist of continuous, time to event, binary, ordered categorical with more than two categories and count data types. For all secondary outcomes that are continuous in nature, they will be analysed using the same statistical method as described for primary outcome.

Binary outcomes: For those secondary outcomes that are binary in nature, data will be summarised as number and percentage of participants in each category by intervention arm. An adjusted relative risk and 97.5% confidence interval will be estimated from a log-binomial regression model and the p-value from the associated model will be produced and used to determine statistical significance. We will also present the adjusted risk difference and the corresponding 97.5% confidence interval.

Ordered categorical outcomes with more than two categories: For those secondary outcomes that are categorical in nature with more than two categories, data will be summarised as number and percentage of participants in each category by intervention arm. An adjusted odds ratio and 97.5% confidence interval will be estimated from an ordered logistic regression model and the p-value from the associated model will be produced and used to determine statistical significance.

Time to event outcome: For those secondary outcomes that are time to event data types, these will be compared between intervention arms using survival analysis methods. Kaplan-Meier survival curves will be constructed for visual presentation of time-to-event comparisons. A Cox proportional hazards model will be fitted to obtain an adjusted hazard ratio and 97.5% confidence interval. The p-value from the associated model will be produced and used to determine statistical significance.

Count data: For those secondary outcomes that are count data type, these will be analysed using a Poisson regression model (or negative binomial regression if there is evidence of overdispersion) with an offset for the length of time the participant was in the trial included in the model, to obtain an adjusted incidence rate ratio and 97.5% confidence interval. The p-value from the associated model will be produced and used to determine statistical significance.

---

### 14.2.3 Planned subgroup analyses

Subgroup analyses will be limited to the same variables used in the minimisation algorithm (see section 6.4.3) and performed on the primary outcome only. The effects of these subgroups will be examined by including an intervention group by subgroup interaction parameter in the regression model, which will be presented alongside the effect estimate and 97.5% confidence interval within subgroups. The results of subgroup analyses will be treated with caution and will be used for the purposes of hypothesis generation only.

### 14.2.4 Missing data and sensitivity analyses

Every attempt will be made to collect full follow-up data on all study participants; it is thus anticipated that missing data will be minimal. Participants with missing primary outcome data will not be included in the primary analysis in the first instance. This presents a risk of bias, and sensitivity analyses will be undertaken to assess the possible impact of the risk. In brief, this will include the use of multiple imputation using chained equations. Further sensitivity analysis will include a per-protocol analysis for the primary outcome only. Full details will be included in the SAP.

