#### 6.4.3 Randomisation Method

Participants will be randomised at the level of the individual in a 1:1:1 ratio to either oral steroid only, intratympanic steroid only, or combined oral and intratympanic steroid treatment. A minimisation algorithm will be used within the online randomisation system to ensure balance in the treatment allocation over the following variables:

- Hearing loss severity pure tone average (PTA) at 0.5, 1, 2 and 4 kHz (mild/moderate less than 70dBHL; severe/profound 70dBHL or greater)
- Time since onset of hearing loss ( $\leq 14$  days;  $> 14$  days)
- New vertigo since onset of hearing loss (participant reported yes; no)
- Site

To avoid the possibility of the intervention allocation becoming predictable, a 'random element' will be included in the minimisation algorithm. Full details of the randomisation specification will be stored in a confidential document at BCTU.

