## 9.1 Loss to follow up definition

Failure to collect primary outcome data at 12 weeks due to participant non-attendance at follow up.

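### Section 14.2.4 removes participants without a 12-week audiogram from the primary analysis, although the repeated-measures model in 14.2.1 is built to use their 6-week audiogram

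*Protocol*

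**What the plan says.** Four parts of the protocol bear on this.

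- **Outcome.** Section 8.2.1 sets the primary outcome as improvement in the four-frequency pure tone average at 12 weeks. Section 8.2.2 makes the same measure at 6 weeks a secondary outcome, also tested by a blinded audiologist.
- **Model.** Section 14.2.1 specifies a repeated-measures mixed-effects linear regression on all assessment times, with time as a category and a time-by-treatment interaction. The 6- and 12-week differences both come from this one model.
- **Missing data.** Section 14.2.4 states: "Participants with missing primary outcome data will not be included in the primary analysis in the first instance". It then acknowledges that this carries a risk of bias, names multiple imputation by chained equations as a sensitivity analysis, and leaves full details to the SAP.
- **What counts as missing.** Section 14.2.4 gives no time point. Section 9.1 defines loss to follow-up as "Failure to collect primary outcome data at 12 weeks due to participant non-attendance at follow up", which places the primary outcome data at week 12.

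**The concern.** A mixed model fitted by likelihood does not need every participant to have every visit. A participant seen at week 6 but not at week 12 contributes the 6-week value and, through the correlation between visits, some information about week 12. The 12-week estimate then remains valid if missing week 12 depends on data already observed, including 6-week hearing.

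Excluding that participant turns the primary analysis into an analysis of those who completed week 12. That is unbiased only under a stronger condition: given the covariates in the model, dropout must not be related to recovery in a way that distorts the comparison between arms. The excluded participants would also leave the 6-week comparison, although the value it needs was measured.

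At stake is the headline estimate. Imputation planned as a sensitivity analysis can show that the headline is fragile, but it does not change the headline.

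**Working it through.** **1. The plan's own figures.** Section 14.1 gives "With 90% power and alpha of 0.025", "to observe a MCID of 10 dBHL with SD of 25 dBHL", and states that "the trial will require 157 participants per arm, or 471 participants in total". Section 14.2 fixes the sidedness: "with two-sided 97.5% confidence intervals".

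- Normal approximation: n = 2 × (2.241 + 1.282)² × 25² / 10² = 155.1, rounded up to 156 per arm.
- Exact noncentral t: 157 per arm, power 90.1%.
- Attrition: 157 / 0.90 = 174.4, rounded up to 175 per arm, 525 in total.

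The stated sample size is reproduced.

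**2. How many participants the rule could remove.** At the planned 10% attrition: 175 − 157 = 18 per arm, or 54 over three arms. How many of these would have a 6-week audiogram is not stated.

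**3. Precision.** Assumptions not in the protocol: correlation ρ between 6- and 12-week improvement of 0.5 to 0.9, and 25% to 100% of those missing week 12 having a 6-week value. With n_c = 157 completers and m participants with week 6 only, the effective number per arm for the 12-week mean under maximum likelihood is

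n_eff = n_c / [1 − ρ² × m / (n_c + m)],

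and power is Φ(10 / (25 × √(2/n)) − 2.241).

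| Case | m per arm | ρ² × m/(n_c + m) | n_eff | Power |
|---|---|---|---|---|
| Completers only | 0 | 0 | 157 | 90.4% |
| ρ 0.5, a quarter have week 6 | 4.5 | 0.25 × 4.5/161.5 = 0.007 | 158.1 | 90.6% |
| ρ 0.7, half have week 6 | 9 | 0.49 × 9/166 = 0.027 | 161.3 | 91.2% |
| ρ 0.9, all have week 6 | 18 | 0.81 × 18/175 = 0.083 | 171.3 | 92.8% |

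The gain over 90.4% is 0.2 to 2.4 points.

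**4. Bias.** Simulation of two arms: 175 per arm, SD 25 dB, true difference 10 dB at both visits, 4,000 runs. Missing week 12 follows a logistic function of the 6-week gain relative to the arm's own mean (intercept −2.55, slope ±0.9 per SD), which gives about 9.6% missing. The random case uses 10%. These dropout patterns are assumed, and baseline covariates are left out.

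| Dropout pattern | ρ | Bias, completers only | Bias, all data, every dropout has week 6 | Bias, all data, half have week 6 |
|---|---|---|---|---|
| Random | 0.7–0.9 | about 0 | about 0 | about 0 |
| Same direction in both arms | 0.7–0.9 | about 0 | about 0 | about 0 |
| Opposite directions by arm | 0.7 | −2.8 dB | about 0 | −1.4 dB |
| Opposite directions by arm | 0.9 | −3.6 dB | about 0 | −1.7 dB |

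Further runs (3,000 replicates, ρ 0.7 to 0.9) with other assumed patterns:

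- The same mechanism in both arms gave completers' estimates of 9.4 to 9.8 dB, a loss of 0.2 to 0.6 dB.
- Opposite directions with milder gradients (14% against 7% missing in one arm, 17% against 7% in the other) gave 8.5 to 8.8 dB.
- Opposite directions with steep gradients (20% against 2%, 28% against 3%), scaled to about 4% dropout overall, gave 8.6 to 8.9 dB.

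**5. The passages side by side.** Section 14.2.1 brings all assessment times into the model. Section 14.2.4 takes out participants for whom one of those times is missing. Section 9.2 allows data gathered before withdrawal to be used in the trial analysis, even when a participant refuses all further collection. On the natural reading, 14.2.4 keeps such data out of the primary analysis whenever week 12 is missing.

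**The case against.** **The exclusion may mean something narrower.** Section 14.2.4 names no time point, section 14.2.1 describes the primary outcome data as gathered at every follow-up visit, and section 9.1 defines loss to follow-up, not the analysis set. The sentence could mean only those with no usable follow-up audiogram. It is also qualified as a first step, with details left to the SAP. This stands as a reason for moderate confidence in the reading. It does not remove the point: section 8.2.1 places the primary outcome at 12 weeks, the sentence is a stated rule and not a silence for the SAP to fill, and if the narrower meaning was intended it still needs rewording.

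**The risk is acknowledged and checked.** Multiple imputation can use the 6-week audiogram, so it is a meaningful check on a completers' analysis. That is fair, but it leaves the primary estimate unchanged.

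**Missing data may be few.** Section 14.2.4 expects them to be minimal, and the pilot's green criterion in section 8.1 is dropout below 5%. Ten per cent is a planning allowance. This stands and limits the size.

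**Stronger readings to avoid.** A reader might infer that the rule breaks the intention-to-treat statement in section 14.2, under which "all participants will be analysed in the intervention group to which they were randomised irrespective of adherence". That sentence concerns the allocated group and adherence, not absent outcomes. Read literally, it would also be broken by any analysis that omits participants with no audiogram. A reader might also infer that about a third of the treatment effect would be lost. That needs recovered participants to miss week 12 in one arm and unrecovered participants to miss it in the other. Nothing in the protocol shows such a pattern. Nor is the trial left short of power, because the 175 per arm already allow for 157 completers.

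**Conclusion.** The point holds as an inconsistency between sections 14.2.4 and 14.2.1 that should be corrected, with moderate confidence that the exclusion is meant to apply at week 12. As written, the primary analysis rests on a stronger missing-data assumption than the chosen model needs, and it sets aside 6-week audiograms that the protocol collects.

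The consequence for the estimate is a risk, not a certainty. The largest figure, about 3 to 3.6 dB against a 10 dB difference, rests on assumed opposite dropout by arm, roughly 10% missing, and correlations of 0.7 to 0.9. Keeping the 6-week data removes bias only under missing at random and only for dropouts who were seen at week 6. If half were not, about half of the bias remains in the extreme case (1.4 of 2.8 dB; 1.7 of 3.6 dB). The precision gain is real but small.

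**What to change.** Replace the exclusion sentence in section 14.2.4 with:

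*All randomised participants with at least one post-randomisation audiogram (6 or 12 weeks) are included in the primary repeated-measures model, in the arm to which they were randomised, under a missing-at-random assumption.*

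Keep multiple imputation as a sensitivity analysis. Any analysis of departures from missing at random can be left to the SAP.

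The cost is a wording change in the protocol, carried into the SAP. It needs no new data, no extra visit and no change to the sample size.
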